### Recruitment and randomization

Patients will be recruited at the time of diagnosis and discussion of the treatment plan after the interdisciplinary tumor conferences of each hospital had finalized the treatment schedule. Written informed consent will be obtained from all participants prior to randomization and baseline visit. Patients can withdraw consent and effectively withdraw their trial participation at any point without any disadvantages. A screening checklist including all inclusion and exclusion criteria will be assessed by a medical doctor prior to randomization. Variable block randomization stratified by tumor entities and study site will be used to randomly assign participants to intervention or control group (1:1). Block length will be disclosed upon completion of the trial. The preparation of the randomization lists will be performed by a statistically trained researcher not involved in the recruitment, allocation, or assessment of the participants. Randomization lists will be uploaded in RedCap and cannot be viewed or changed during the trial. Group allocation will be performed over the RedCap database. Patients will be allocated after obtaining consent and completing baseline assessments to confirm eligibility.

### Eligibility criteria

Adult female patients with histologically confirmed gynecological cancers (ovarian, breast, cervical or uterine) are eligible to participate in this study. Potential trial participants will be identified through interdisciplinary tumor conferences at both study centers and potential study participation will be documented in the protocol. A complete list of inclusion and exclusion criteria can be found in **Table 2**. Exclusion criteria were chosen to minimize the risk for critically ill patients as well as to exclude diseases significantly impacting the normal metabolism.

**Table 2 T2:** Inclusion and exclusion criteria of the study.

Inclusion criteria	
	◼ Women with histologically confirmed ovarian (including peritoneal cancer or cancer of the fallopian tubes), breast, endometrial or cervical cancer ◼ ≥ 18 years of age
	◼ BMI ≥ 19 kg/m^2^ ◼ ECOG 0-2 at baseline ◼ Anticipated life expectancy of > 6 months ◼ Planned to receive intravenous chemotherapy for at least three months ◼ Planned to receive chemotherapy including at least one topoisomerase inhibitor or alkylating agent
	◼ Ability to understand nature and effects of the trial participation
Exclusion criteria	
	◼ Simultaneous radiation therapy ◼ Received Chemotherapy in the last six months ◼ Weight loss of >10% in the last three months ◼ Type I diabetes or intensified insulin treatment
	◼ Kidney failure (creatinine above 2mg/dl), liver failure (liver enzymes above 2,5x the upper limit of normal)
	◼ Current or past eating disorders ◼ Other psychiatric diseases
	◼ Myocardial infarction, stroke or pulmonary embolism within the last 3 months
	◼ Unstable heart disease ◼ Severe internal co-morbidities
	◼ Enterostomy, short bowl syndrome
	◼ Pregnancy & breastfeeding period
	◼ Participation in another interventional trial likely to interfere with the study outcome ◼ Language difficulties

### Study intervention and control

All participants will receive a teaching by a registered dietician as well as a pamphlet on dietary tips to cope with CHT related adverse events.

#### Intermittent fasting group

To increase the feasibility of IF during CHT, the intervention group will be asked to follow an IF schedule of at least 16 h continuous fasting per day on a minimum of five days per week. This allows a disruption of the fasting due to chemotherapy-related issues or to accommodate everyday events such as birthdays or short visits in the IF schedule. We have successfully tested this fasting routine in a pilot study of healthy volunteers, where ketone bodies reached the desired concentration after 16 hours of fasting. We found IF to be safe and effective in reducing fatigue and increasing QoL even in healthy volunteers. The IF schedule was feasible in a stressful work environment and variable working hours during shift work (9). To ensure the positive benefits during the administration of CHT, participants will be required to adhere strictly to the 16h fasting period per day from two days before until one day after the administration of i.v. CHT. To prevent possible negative effects from reversing the metabolic switch to an anabolic state once eating again, no food intake will be allowed on the day of CHT. On the remaining time period of the cycle, the two days of non-fasting per week are allowed. The 16-hour continuous fasting interval can be started at any time point each day. While adhering to the same fasting schedule each day is recommended (e.g., fasting in the morning) to establish behavioral manners, this is not compulsory. Non-sugary drinks including water, tea or coffee without milk (soy milk, oat milk, cow milk etc.), as well as clear vegetable broth are allowed during the 16h fasting period. Within the non-fasting period of 8 hours per day no dietary restrictions will be given. However, a normo-caloric Mediterranean diet are recommended for all patients. Participants of the intervention group will receive a 20-minutes one-on-one counselling by a licensed dietician.

#### Control group

The control group will not be given any dietary restrictions. A normal-caloric Mediterranean diet is encouraged and a personal counseling session with a licensed dietician will be provided before starting CHT for every participant of the control group.

### Adherence

To increase compliance, all participants will be offered assistance with any problems related to fasting and adherence at each planned study visit. Furthermore, all participants will receive written information on dietary advice and the management of CHT-related gastrointestinal toxicities. Individual diet-specific questions can be discussed with a medical doctor at any time during the study in person or via electronic communication. Adherence will be measured through a specifically designed simple daily diary (three smiley system) and the hydroxybutyrate level in the blood (assessed at day 1 of every cycle). To increase long-term practicability in everyday life (e.g. shift work, family events) and to allow for adjustments to individual lifestyles, participants of the intervention group can break the IF diet for up to two days per week (five days fasting, two days off).

### Baseline characteristics

For eligibility screening and baseline assessments, data of potential trial participants including full oncologic history, vital signs, anthropometric measurements, full medical history, concomitant therapies, pre-existing adverse events from prior chemotherapy as well as full inclusion and exclusion criteria will be recorded. Once recruited for the trial, all participants will be asked to complete questionnaires measuring current QoL and baseline laboratory checks will be performed (see **Table 1**).

### Outcome measures

#### Primary outcome

Primary outcome of this study is the difference of the mean change in fatigue from baseline to last follow-up time point of the active trial period (3 months) between the IF group and the control group. A variation of up to ± 1 week for trial termination is allowed due to potential delays of CHT (e.g. due to insufficient blood values or public holidays).

Fatigue is measured after each chemotherapy treatment using the Functional Assessment of Chronic Illness Therapy-Fatigue Scale (FACIT- FS©). This questionnaire assesses cancer therapy related fatigue. It is part of the FACIT-F© questionnaire (22) which is a combination of the Functional Assessment of Cancer Therapy general core questionnaire (FACT-G©) and the FACIT-FS©. The FACIT-FS© includes 13 fatigue related questions, which are rated on a 5-point Likert scale (not at all to very much) over the last 7 days. Scores will be calculated according to published scoring algorithms.

#### Secondary outcomes

As there is only very limited availability of data regarding fasting during CHT, a broad range of secondary endpoints for future confirmatory clinical trials will be assessed. A detailed overview of the assessed outcomes at each time point is summarized in **Table 1**.

#### Quality of life

General QoL and overall health as measured by the two general wellbeing items of the European Organization For Research and Treatment Core Quality of Life Questionnaire (EORTC QLQ-C30 version 3.0© will be assessed. Furthermore, the FACT-G© questionnaire to assess cancer therapy associated QoL, as well as QoL questionnaires specific to gynecologic cancers FACT-B© (breast cancer), FACT-O© (ovarian cancer), FACT-EN© (endometrial cancer), FACT-CX© (cervical cancer)) will be completed by the patients to assess the effects of IF on QoL. The FACT-G© questionnaire forms the core of the FACT questionnaires and is complemented by the specific cancer type related questionnaire. Items relate to disease-, treatment- and condition-related QoL. Scores will be calculated according to published scoring algorithms by the FACT© association. As sleep quality and pelvic floor deficiencies are often related with gynecological cancers and CHT, these aspects will be assessed separately by validated questionnaires. Sleep quality will be examined through the Pittsburgh Sleep Quality Index, a short questionnaire consisting of 19 items, which can be summed up in seven different components of sleep quality such as sleep duration, sleep efficiency, disruptions of sleep, etc. (23). Pelvic floor deficiencies will be assessed with the German pelvic floor questionnaire, which includes items regarding sexual function, bladder and bowl disorders and associated QoL (24).

#### Feasibility and adherence

Due to the limited evidence currently available on fasting during CHT, we will assess the feasibility of the proposed IF schedule during CHT by recording adherence to the diet in a simplified daily diary (three smiley system), as well as the number of major protocol violations and discontinuations of the trial at each study visit.

#### Body weight changes and safety

To assess the safety of IF during CHT, during which many patients struggle to maintain their weight, changes in BMI will be recorded and compared between groups. Furthermore, regular laboratory assessments of blood values such as hematograms, liver and kidney function will be assessed over the study period. A detailed overview of laboratory values assessed can be found in **Appendix A**. Laboratory values will be accepted if obtained ± 1 day of the planned assessment day (e.g. one day prior to CHT).

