## Methods

### Study design and setting

This study is designed as a prospective, two-arm parallel-group, multi-center, open-label, randomized-controlled clinical trial (phase III trial). It will be conducted at the Department of Gynecology and Obstetrics of the University Medical Centre of the Johannes Gutenberg University Mainz, Germany, as well as the department of Gynecology and Obstetrics at the St. Josef’s Hospital, Wiesbaden, Germany. All data will be recorded pseudonymized. Only the principle investigator of the study, as well as the study nurses in charge will have access to the pseudonymization list in case of adverse events or trial termination.

The active fasting period will be conducted for three months during CHT. Participants will be scheduled for study visits during their routine care (d1 of each cycle) and routine laboratory visits on days 8 (and 15 in three week cycles) of each cycle during the three months of the active trial period. Additional study visits will be scheduled for nutritional counseling prior to the start of the chemotherapy as well as a follow up visit at six months (**Table 1**). QoL including fatigue assessment will be performed at baseline, each week during the 12 weeks active trial period as well as at the six months follow-up. Specific quality of life aspects regarding sleep quality and pelvic floor function will only be assessed at baseline, after three months and after six months.

**Table 1 T1:** Visit overview and outcome measures assessed during each study visit.

Timepoint	Study period						
	t_-1_ *(3d - 4w prior to CHT)*	All cycles d_1_	All cycles d8	3-week cycles day 15	12 weeks after Start CHT ( ± 1 week)	Post surgery where applicable	6 months follow up ( ± 2 weeks)
Enrolment Eligibility screen Informed consent Randomization Allocation	XXXX						
Interventions Intermittent fasting Normal diet Nutritional counselling	XXX				→ →		Voluntary continuation of IFSwitch to IF possible
Assessments Demographics Medical history Current medication Anthropometric measurements Vital signs Physical examination CTCAE Hematogram Glucose/ketone levels Organ Blood panely-H2AX DNA damage essayImmunological responseTumor response Tumor markers Pathological response Radiological response	XXXXXXXXXXX(X)^3^	XXXXXXXXX^1^	XX^2^	X	XXXXXXXXX(X)	X	XXXXXXXX(X)

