Questionnaires *Fatigue → FACIT-FS©General QoL → FACT-G© General wellbeing → EORTC QLQ-C30© TOI mental health TOI physical healthTumor specific FACT-B© FACT-O© FACT-Cx© FACT-En©Pelvic floor functionalitySleeping qualityAdherence diary Continuation/Acceptance/ Difficulties		XXXXXXXXXX^4^X^5^X^6^	XXXXXXXXX	XXXXXXXXX	XXXXXXXXXXXX →		XXXXXXXXXXX

* Some questionnaires can be calculated as subgroups from other questionnaires. Thus, only 2-3 questionnaires will need to be completed by the participants.

^1^ y-H2AX DNA damage essay will only be performed on the day of chemotherapy at cycle 1 day 1, after 6 weeks and after 12 weeks.

^2^ The immunological response will only be assessed at baseline (day of enrollment), as well as one week after chemotherapy is given at three time points (week 1, week 7 and week 13).

^3^ Radiological response will only be assessed in patients treated neoadjuvantly for ovarian/peritoneal or cancer of the fallopian tubes (response rate to neoadjuvant CHT), as well as in metastasized patients of all included tumor types.

^4^ Pelvic floor functionality will only be checked on day 1 of cycle 1; 12 weeks after the start of chemotherapy and during the 6 month follow-up.

^5^ Sleeping quality will only be checked on day 1 of cycle 1; 12 weeks after the start of chemotherapy and during the 6 month follow-up.

^6^ Adherence will only be checked via a daily diary in the intermittent fasting group.

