### Statistical analysis

Patients will be randomized to the intervention or control group (1:1) stratified by tumor entity and study site. The primary endpoint, the difference of the mean change of fatigue over a period of three months as measured by the FACIT-FS© score, will be compared between both groups using mixed models. Confounders such as age, type of CHT, neoadjuvant/adjuvant vs metastatic treatment, the Eastern Cooperative Oncology Group performance status (ECOG), histological tumor grade, and Fédération Internationale de gynécologie et d’Obstetrique (FIGO) -stage will be included in the mixed models. Laboratory data, as well as QoL questionnaire-based outcomes will also be assessed using mixed models. Missing data for the primary outcome as well as secondary outcomes with the potential to become main outcomes in subsequent larger trials will be imputed. Where possible, missing questions from FACT^©^ questionnaires will be prorated using the average of the other answers in the subscale (prorated subscale score = [sum of the item scores]*[N of items in subscale]/[N of items answered]) as long as more than 50% of the items are answered. Data will be imputed by drawing values from the distribution of the control group (jump to reference).

A comprehensive summary will be given for primary and secondary endpoints, including absolute and relative frequencies for categorical and binary variables as well as mean and standard deviation or median and interquartile range and minimum-maximum for all data with at least interval scale level. Pathological response rates after neoadjuvant CHT will be compared using the Chi square test. Radiological response rates (complete response, partial response, stable disease, and progressive disease) will be compared between the arms at 3 months and 6 months using the Mann-Whitney-U-tests. The occurrence of any adverse event as well as the occurrence of grade 3 or higher adverse events will be compared between both groups using the Chi square test. And a list of immunological and metabolic parameters will be compared between both groups using the Mann-Whitney-U test. A paired Wilcoxon test will be used to compare the change in BMI over three months between both groups.

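### Weight appears to be taken on chemotherapy days, when only the fasting arm is barred from eating, so a three-month BMI change from the pre-treatment weight would carry a small fasted-versus-fed difference

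*Protocol article*

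**What the plan says.** Body weight is followed as a safety outcome: "changes in BMI will be recorded and compared between groups" (Protocol article, Body weight changes and safety). The Statistical analysis section adds: "A paired Wilcoxon test will be used to compare the change in BMI over three months between both groups". It does not name the starting weight.

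On timing, Study design and setting states: "Participants will be scheduled for study visits during their routine care (d1 of each cycle"), and Table 1 gives week 12 a column of its own with a window of ±1 week. Footnote 1 to Table 1 says that the DNA damage assay "will only be performed on the day of chemotherapy at cycle 1 day 1, after 6 weeks and after 12 weeks". The section on immunological response schedules a sample at week 13, seven days after chemotherapy.

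On food, the Intermittent fasting group section says that "no food intake will be allowed on the day of CHT". Fluids are permitted: non-sugary drinks and "clear vegetable broth are allowed during the 16h fasting period". For the other arm: "The control group will not be given any dietary restrictions" (Control group).

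On baseline, the Baseline characteristics section lists: "For eligibility screening and baseline assessments, data of potential trial participants including full oncologic history, vital signs, anthropometric measurements". Table 1 places this visit 3 days to 4 weeks before chemotherapy, and Recruitment and randomization places allocation after it.

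**The concern.** A difference in change scores is interpretable only if the conditions of weighing are alike in the two arms, or if any unlikeness is the same at both ends of the change. Here the stated visit and food rules seem to put the follow-up weight on a day when one arm has an empty stomach by design and the other need not. The pre-treatment weight is taken before allocation, when no arm-specific food rule applies.

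An artefact of this kind always points the same way, towards more apparent weight loss under IF, and neither randomisation nor a larger sample removes it. It would affect the only weight comparison that the article plans, on an outcome meant to show whether IF is safe for patients who already find it hard to keep their weight. The same readings would be set against the BMI figure of 18 kg/m² in the section on trial termination, which lies 1 kg/m² below the entry limit of 19.

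**Working it through.** **1. Is weight taken on chemotherapy days?** The row alignment of Table 1 is lost in the text at hand. The column for day 1 of all cycles holds nine marks, the last carrying footnote 1 (the DNA damage assay). Nine rows run from current medication to that assay, and anthropometric measurements are among them. That is good but indirect evidence. For week 12, footnote 1 ties the 12-week blood draw to the day of chemotherapy, and a week-13 sample seven days after chemotherapy points to the same day. The ±1 week window means that some patients may be weighed on another day.

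**2. When does the difference survive?** Let g be the average drop in measured weight when an IF patient is weighed without food that day, compared with a control who may have eaten. W0, W1 and W12 are the weights that would be read at the pre-treatment visit, cycle 1 day 1 and week 12 if both arms were in the control state.

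- From the pre-treatment weight: IF change = (W12 − g) − W0; control change = W12 − W0. The arm difference is the true effect minus g.
- From cycle 1 day 1: IF change = (W12 − g) − (W1 − g) = W12 − W1; control change = W12 − W1. The arm difference is the true effect, and g cancels as far as it is the same on both days.

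So the point turns on the starting weight, which the article leaves open.

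**3. The plan's own figure.** The only stated sample size is for fatigue: difference 9.1, SD 13.7, power 90%, two-sided 5%. By the normal approximation n = 2 × (1.960 + 1.282)² × 13.7² / 9.1² = 47.6, so 48 per group, as stated. The exact t-test gives 48.6 and a power of 0.896 at 48. No figure is given for BMI; 48 per arm is used below only as the number expected to be analysed.

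**4. Size of the shift (assumed inputs).** The documents give no meal weight, height or SD of BMI change. With height 1.65 m, height² = 2.72 m² and BMI shift = g / 2.72:

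| Assumed g (kg) | BMI shift (kg/m²) |
|---|---|
| 0.3 | 0.11 |
| 0.5 | 0.18 |
| 1.0 | 0.37 |

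Against the 1 kg/m² between 19 and 18, this is 11% to 37%.

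**5. Effect on a test with no true weight difference.** Standard error = SD × √(2/48): 0.204 for SD 1.0 and 0.306 for SD 1.5. Noncentrality = shift / standard error, with 94 degrees of freedom. Two-sided rejection at a nominal 5%:

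| BMI shift | SD 1.0 | SD 1.5 |
|---|---|---|
| 0.11 | 8% | 7% |
| 0.18 | 15% | 9% |
| 0.37 | 43% | 22% |

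The calculation uses an independent-groups t-test as a stand-in; the article names a Wilcoxon test, so the rates are indicative.

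**The case against.** The strongest reply is that how patients are weighed is operational detail. The ethics statement refers to a full protocol, version 4.0, which is not shown and may standardise weighing. If it does, the matter is closed. But the point does not rest on silence alone: a site that followed the visit days and food rules as published would produce the difference.

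Second, the starting weight is not fixed. The article uses the word baseline for sleep and pelvic floor assessments that footnotes 4 and 5 place on cycle 1 day 1. A change from that day to week 12 fits the text, and on it the difference largely goes. This stands, and it is why the conclusion is conditional.

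Third, a week-12 infusion is not guaranteed. Four three-week cycles would start at weeks 0, 3, 6 and 9, and footnote 1 governs the assay, not the scales. This also stands; it would dilute the difference.

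A reader might go further and infer that the comparison is certainly biased, by 0.5 to 1.5 kg of gut content and lost water, with false rejection up to 76%. The documents do not support that. Fluids and broth are allowed while fasting, some controls may be weighed before eating, and 76% needs the largest assumed gap (1.5 kg, or 0.55 kg/m²) together with the smallest assumed SD (1.0).

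Finally, secondary outcomes are declared exploratory, and the direction of the error exaggerates harm from IF instead of hiding it. Both are true and limit the importance of the point.

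**Conclusion.** The point holds in conditional form. The published rules appear to put on-treatment weighing on days when the arms differ in food intake by design. If the three-month BMI change starts from the pre-treatment weight, it overstates weight loss under IF by an amount that the documents do not give: about 0.1 to 0.4 kg/m² for an assumed gap of 0.3 to 1.0 kg at 1.65 m. With 48 per arm and an assumed SD of change of 1.0 to 1.5 kg/m², that would turn a nominal 5% test into one that rejects in about 7% to 43% of trials without a true effect. The lower end is the more plausible. If the change starts from cycle 1 day 1, little of this remains.

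The conclusion rests on a count of marks in a damaged table for day-1 anthropometry, and on week 12 falling on a chemotherapy day for most patients. The primary endpoint is not affected. No position is taken on the food rule or on the BMI threshold. The severity is minor.

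**What to change.** Weigh both arms on arrival, before any food that day, at the baseline visit, on day 1 of each cycle and at week 12. Record the hours since last calories at each weighing. State which weight starts the three-month change, and compute that change between weights taken in the same state: for example cycle 1 day 1 to week 12, at least as a sensitivity analysis.

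The cost is one visit instruction and one form field. Controls would wait to eat until weighed on visit days. If that is unwelcome, the recorded hours alone would still support a sensitivity analysis. Some difference would remain, because IF patients will usually have fasted longer before arrival than controls after an ordinary night. The instruction should be in place before weighing starts, because fed or fasted state cannot be recovered reliably afterwards.
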